### Outcomes

The primary outcome was all-cause mortality during hospital admission.

Secondary outcomes were identified *a priori *as relevant to specific poisons since different complications were expected according to the poison ingested. For pesticides, secondary outcomes included: (i) proportion of patients requiring intubation; (ii) total period of time ventilated; (iii) time to first ventilation; and (iv) seizures. For yellow oleander poisoning, the secondary outcome was the proportion of patients with cardiac dysrhythmias requiring anti-digoxin Fab (indications: 3° heart block, Mobitz type II 2° block, sinus bradycardia with heart rate <35 bpm, and sinus arrest or block with sinus pauses >3 secs) or serum potassium greater than 6.0 [23]. Unfortunately, anti-digoxin Fab became unavailable after four months [24] and patients were then transferred to tertiary cardiac centres for temporary pacing. Transfer used the same criteria and therefore this secondary outcome become a combination of receiving anti-digoxin Fab or transfer for tertiary care.

All secondary outcomes were reviewed twice a day at the review ward rounds. Any events not recorded at the time they occurred were recorded at this ward round.

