### Patient management

All patients are seen on admission to the medical wards or, in Kurunegala, after admission to the Emergency Treatment Unit (emergency department). There the patients were resuscitated as necessary by wards doctors together with study doctors. The patient's airway was stabilised and oxygen, atropine, fluids, and antidotes given as necessary.

Gastric decontamination was only started when patients were stable. The original protocol stated that patients would receive neither gastric lavage nor forced emesis. However, at the request of the consultant physicians caring for the patients, from June 2003 patients who presented within two hours of ingestion of a potentially serious poison received a brief gastric lavage (3 × 300 ml of water). Many patients received either gastric lavage or mechanical forced emesis in the peripheral hospital transferring the patient before admission to the study hospitals.

Patients remained under the care of the hospitals' consultant physicians using management protocols agreed between the consultants and study team [22]. The ward medical teams made decisions about intubation and transfer of patients to intensive care or for cardiac pacing independently of study doctors. All decisions were made on the basis of clinical condition and do not reflect the poison ingested or the charcoal allocation.

Patients were seen regularly by full time study doctors at least every three hours and more often according to clinical need, 24 hrs a day. Patients were also seen on a study ward round twice each day (0830, 2030) at which time their condition was recorded in a handheld computer using a specially written database. Significant events (intubation, seizures, death) were recorded at the time of the event. The patients' condition over the previous 12 hrs was reviewed at each ward round.

Patients were first managed on the medical ward. Seriously ill patients, as judged by the medical team, were then transferred to the intensive care unit (ICU) as a bed became available. Each hospital had 2–8 ICU beds for medical patients; many were filled with OP poisoned patients and there was usually a delay in obtaining a bed.

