### Sample size

In both hospitals, at least 10% of poisoned patients die before discharge [1]. An absolute reduction of 3% will be clinically important. In order to be able to detect whether either regimen of activated charcoal reduced the death rate from 10% to 7%, with a significance level (alpha) of 5% and a power of 80%, a minimum of 1400 patients had to be recruited to each arm of the trial (i.e. 4,200 patients in total).

Sample size calculations were based on current practice and a case fatality rate of 10%. The Independent Data Monitoring and Ethics Committee (IDMEC) was asked to review the recruitment and event rates during the first year of the trial in order to make recommendations about expanding the trial by including further hospitals if necessary.

There should have been no loss to follow up for the primary outcome. Patients were either discharged alive from the wards or their bodies transferred to the morgue for judicial autopsy. All secondary outcomes were assessed in hospital before discharge.

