### Statistical analysis

The main analysis will be carried out on an intention-to-treat basis, using the chi -squared test for the primary outcome (or Fisher's exact test if appropriate) and for other dichotomous outcomes. Odds ratios (plus 95% confidence intervals) will be reported to establish magnitude and direction of the treatment effect. In the original protocol, we indicated that risk would be the chosen measure of effect; however, in order to be able to adjust the treatment effect estimate for stratification variables in future analyses, we will calculate odds instead, using logistic regression. Since the primary outcome is an uncommon event, risk and odds should be similar.

For outcomes where time-to-event is recorded, we will use the logrank test to compare treatment groups, produce Kaplan-Meier curves to illustrate the comparison, calculate incidence rates and perform Cox's regression to estimate hazard ratios, adjusted for stratification factors.

An analysis of trends in treatment effect for factors 'reported time from ingestion to treatment' and 'patient status on admission' will be performed.

It is possible that both treatment regimens, if effective in reducing case fatality rates, will be more effective the earlier they are started. Therefore we will assess the trends in clinical effectiveness according to time post-ingestion to start of therapy using statistical modelling techniques. In order to determine whether treatment should be started irrespective of severity, we will likewise also assess trends in case fatality rates across a gradient of severity.

Admission blood samples will be retrospectively analysed to determine the identity of the poison ingested. The primary analyses will be repeated using the confirmed identity of the poison.

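### The oleander secondary outcome was changed from meeting clinical criteria to receiving Fab or transfer, so a patient who qualifies but dies or is not moved first counts as event-free

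*Protocol article*

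**What the plan says.** In the Outcomes section, "the secondary outcome was the proportion of patients with cardiac dysrhythmias requiring anti-digoxin Fab", followed by a list of rhythm indications and a serum potassium threshold. This describes a patient's state. The section then reports that "anti-digoxin Fab became unavailable after four months" and that patients were afterwards sent to tertiary cardiac centres for pacing. Because the transfer criteria were the same, it says, "this secondary outcome become a combination of receiving anti-digoxin Fab or transfer for tertiary care". This describes care delivered.

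Death is handled separately: "The primary outcome was all-cause mortality during hospital admission". The article gives no rule for a patient who meets the oleander criteria and dies, or stays on the ward, without Fab or transfer.

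On who decides, the Patient management section says: "The ward medical teams made decisions about intubation and transfer of patients to intensive care or for cardiac pacing independently of study doctors". It adds that these decisions rested on clinical condition and did not follow the charcoal allocation. The Statistical analysis section compares arms "using the chi -squared test for the primary outcome (or Fisher's exact test if appropriate) and for other dichotomous outcomes", with odds ratios reported.

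**The concern.** The step from the first definition to the second rests on the criteria being unchanged. Unchanged criteria mean that the threshold for transfer matches the threshold for Fab. They do not mean that everyone who crossed the threshold was treated or moved. To be transferred, a patient has to live until the move. Someone who qualifies and dies on the ward has one of the worst courses in the trial, yet is placed with the patients who never developed a serious dysrhythmia.

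The error need not be equal across arms. The trial's hypothesis is that charcoal reduces death. If it does so among qualifying oleander patients, more of them survive to be transferred in the charcoal arms, and the event rate there rises because of the benefit.

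This is the only secondary outcome specific to oleander. The Background puts oleander at around 30% of recruits, and says that the monitoring committee recommended continuing so that an earlier oleander result could be verified independently. Recruitment ran from 31 March 2002 to October 2004, about 31 months, so transfer was the operative route for roughly 31 − 4 = 27 of them.

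**Working it through.** **Plan's own figure.** The article gives no expected rate, effect or power for the oleander outcome, so there is nothing to reproduce. The Sample size section (10% v 7%, 1,400 per arm) concerns deaths from all poisons. It is used below only to bound one assumption.

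**Inputs.** From the article: about 30% oleander, more than 4,500 recruited, 1:1:1 allocation. Hence 0.30 × 4,500 = 1,350 oleander patients, or 450 per arm. All other rates are assumed.

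**Formula.** In each arm let c be the share meeting the criteria, and m the share meeting them but dying before Fab or transfer. Survivors who qualify but are never moved are set to zero here for simplicity; they would also score as event-free.

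- Rate as written = c − m.
- Difference as written (charcoal minus control) = true difference in c + (m control − m charcoal).

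The bias in percentage points therefore equals the reduction in pre-transfer deaths, and it runs against charcoal. A true benefit reverses only when 0 < c control − c charcoal < m control − m charcoal.

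**Cases (control v charcoal).**

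| Criteria met | Die first | True OR | Reads as | OR as written |
|---|---|---|---|---|
| 10% v 10% | 4% v 2% | 1.00 | 6% v 8% | 1.36 |
| 20% v 18% | 1% v 0.7% | 0.88 | 19.0% v 17.3% | 0.89 |
| 20% v 18% | 5% v 3.5% | 0.88 | 15.0% v 14.5% | 0.96 |
| 20% v 18% | 10% v 7% | 0.88 | 10.0% v 11.0% | 1.11 |

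First row: (0.08/0.92)/(0.06/0.94) = 1.36. Last row: (0.11/0.89)/(0.10/0.90) = 1.11, against a true (0.18/0.82)/(0.20/0.80) = 0.88. Reversal occurs there because 2 points is less than 3 points. That row places every death, at the all-poison design rates, before transfer, so it is an upper bound.

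**Range with the criteria rate equal in both arms.** With 8% to 15% qualifying and deaths of 2% to 6% halved by charcoal, the odds ratio as written runs from 1.09 (13% v 14%) to 2.58 (2% v 5%). The true value is 1.00 throughout.

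**Range with an effect on the criteria.** I varied c in controls (10%, 15%, 20%, 30%), its risk ratio (0.95, 0.90, 0.85, 0.80, 0.70) and m (1% v 0.7%, 3% v 2.1%, 5% v 3.5%, 10% v 7%). Of the 80 combinations, 75 are feasible. The direction reversed in 12, all with a risk ratio of 0.85 or higher and m of at least 3% v 2.1%. Most of the rest moved towards 1. At a risk ratio of 0.70, where c and m fall in the same proportion, there was almost no distortion. The 12 of 75 counts grid cells and is not a probability.

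**With the outcome scored on criteria or death.** The deaths modelled are a subset of those who qualified, so the table returns to 10% v 10% (OR 1.00) and 20% v 18% (OR 0.88).

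**The case against.** *A reversed effect has not been shown.* A reader might infer from the 1.36 that the definition turns benefit into harm. It does not show that: with equal criteria rates the truth is a null, and the illustration shows a null drifting. True reversal needs a weak effect on the criteria together with appreciable deaths before transfer. This objection stands.

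*The large figures are remote.* The 2.58 requires 6% of 8%, or 75%, of qualifying controls to die first, which nothing in the article supports. Even the 1.36, as 27 v 36 events in 450 each, has standard error √(1/27 + 1/423 + 1/36 + 1/414) = 0.264 on the log scale. Its 95% interval is about 0.81 to 2.28, so it would not be read as evidence against charcoal. This stands too.

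*Biased referral.* Since the trial is open and ward teams decide on transfer, a reader might infer that transfer was influenced by allocation. The Patient management section says that it was not, and nothing in the article contradicts this. The inference is unsupported and should not be made. Impartial referral does not, however, remove the problem of death before transfer.

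*The deaths are not lost.* They count in the primary outcome, and oleander is a pre-specified subgroup for it. That limits the harm, provided the two results are read together. It does not correct the secondary outcome.

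*A statistical analysis plan might settle it.* It might, but the article states a definition, and as stated that definition classes these patients as event-free.

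**Conclusion.** The point holds in a limited form. The redefinition replaces qualifying with being treated or moved, and the ground given does not make the two equal. If charcoal reduces deaths among qualifying patients before Fab or transfer, the comparison is biased against charcoal. Usually a benefit is diluted or a null drifts above 1; reversal is possible only under the condition shown above. The size cannot be determined, because the article gives neither the share of oleander patients who qualified nor the number who died first. If such deaths are about 1%, the effect is negligible (0.89 against 0.88). The defect affects one poison-specific secondary outcome and leaves the primary outcome intact. It still merits correction, because the rule counts clear failures as successes.

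**What to change.** For the whole trial, score an oleander patient as having the outcome if any rhythm or potassium criterion already listed in the Outcomes section was met in hospital, whether or not Fab or transfer followed. Also count death before Fab or transfer as an event, so that a patient with incomplete rhythm or potassium records who died is not scored as a success. Report the components by arm. Report receipt of Fab or transfer separately, labelled as care received.

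The cost is a revised sentence in the definition and a re-derivation from the event and twice-daily ward-round records. There are two downsides. The outcome then overlaps with the primary outcome through death; reporting the components lets the reader see the criteria-only result. And rhythm or potassium records for untransferred patients may be incomplete: the article does not say that these were recorded for everyone, and with recruitment closed they cannot be collected afresh. The number of untransferred patients without usable records should be given by arm.

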### Sample size

In both hospitals, at least 10% of poisoned patients die before discharge [1]. An absolute reduction of 3% will be clinically important. In order to be able to detect whether either regimen of activated charcoal reduced the death rate from 10% to 7%, with a significance level (alpha) of 5% and a power of 80%, a minimum of 1400 patients had to be recruited to each arm of the trial (i.e. 4,200 patients in total).

Sample size calculations were based on current practice and a case fatality rate of 10%. The Independent Data Monitoring and Ethics Committee (IDMEC) was asked to review the recruitment and event rates during the first year of the trial in order to make recommendations about expanding the trial by including further hospitals if necessary.

There should have been no loss to follow up for the primary outcome. Patients were either discharged alive from the wards or their bodies transferred to the morgue for judicial autopsy. All secondary outcomes were assessed in hospital before discharge.

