## Methods/design

The study was designed as an open RCT with three parallel groups: multiple dose charcoal vs single dose charcoal vs no charcoal in Sri Lankan adult patients presenting to a secondary hospital with a history of acute self-poisoning. From May 2004, an RCT of pralidoxime in symptomatic organophosphorus pesticide poisoned patients (ISRCTN55264358) was nested into this study.

The principal research question to be addressed was whether activated charcoal, either as a single or multi-dose regimen, will reduce the rate of death and complications following acute poisoning.

The trials were drawn up using the MRC's clinical trial proforma and were designed to be compliant with the CONSORT statement [21].

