**Figure 1 F1:**
[figure not shown]
The hand held computer used to recruit and randomise patients and to record all events. Randomisation was performed at the patient's bedside. Allocation could not be predicted by the study doctor.

The allocation sequences were generated independently by the study statistician (EJ) and implemented by the programmer (SA), neither of whom had a role in patient recruitment, treatment or assessment. Variable block sizes of 3, 6 and 9 were used to allocate patients in equal numbers to each treatment group i.e. ratio 1:1:1 using Stata v7 software (ralloc subroutine version 3.2.5).

Participants were recruited and randomised by a study doctor at the bedside using a dedicated handheld computer at each study hospital (Figure 1). Randomisation occurred after the patient's baseline data had been entered and receipt of consent noted, and could not be manipulated by study doctors. The recruiting doctor was unable to predict allocation before randomisation.

All practical steps were taken to avoid bias: (i) the randomisation program was designed to be rapid and simple to operate, and yet remain independent of the investigators; (ii) the next treatment allocation could not be predicted in advance; (iii) the primary outcome, vital status at discharge, was unambiguous, and the secondary outcomes were objective; (iv) all outcomes were recorded systematically by the study team, not other hospital physicians; (v) patient follow-up was expected to be near 100% complete; and (vi) the analysis will be performed on an intention-to-treat basis.

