### Study hypotheses and principal comparisons

The main hypothesis is that multi-dose activated charcoal will reduce the case fatality rate from 10% to 7%, hence the first principal comparison will be multi-dose activated charcoal versus no intervention. The potential of multidose regimens to work long after ingestion – due to interruption of enterohepatic circulation and gut dialysis – means that such a regimen is more likely to work in a situation where people typically present several hours after ingestion.

We suspected that a single dose of charcoal would be less effective since most poison absorption will have taken place by the time the patients present to hospital. Therefore, the second principal comparison will test the hypothesis that the case fatality rate in patients receiving a single dose of activated charcoal is equal to that in patients receiving multiple doses.

In order to investigate whether a single dose of activated charcoal has a similar effect as giving no intervention, the third principal comparison will test the hypothesis that the case fatality rate in patients receiving a single dose of activated charcoal is equal to that in patients receiving no intervention.

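### The sample size asks about either regimen at one 5% alpha, the hypotheses make multi-dose versus none the main test among three principal ones, and the order of testing has no stated consequence

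*Protocol article*

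**What the plan says.** The protocol article describes the trial's main claim in two ways.

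- **Either regimen.** Methods/design gives the principal research question as "whether activated charcoal, either as a single or multi-dose regimen, will reduce the rate of death and complications following acute poisoning". Sample size follows suit: the trial should "detect whether either regimen of activated charcoal reduced the death rate from 10% to 7%, with a significance level (alpha) of 5" per cent and 80% power, for which "a minimum of 1400 patients had to be recruited to each arm of the trial (i.e. 4,200 patients in total").
- **Multi-dose first.** Study hypotheses and principal comparisons makes the fall from 10% to 7% under multi-dose charcoal the main hypothesis, "hence the first principal comparison will be multi-dose activated charcoal versus no intervention". The Abstract agrees: the study was set up to compare multi-dose with no charcoal, and the single-dose arm was added to show whether any multi-dose benefit came from the first dose or from all of them.

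The hypotheses section then adds single versus multiple dose as the second principal comparison and single dose versus none as the third. It does not make any comparison depend on an earlier one. Statistical analysis specifies a chi-squared (or Fisher's exact) test and odds ratios with 95% confidence intervals, and mentions no gate, global test or adjustment.

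**The concern.** A 5% alpha has to belong to a defined claim. On the first description, a single-dose effect alone would answer the principal question. On the second, the single-dose comparisons explain a multi-dose benefit and have little confirmatory role without one. The two descriptions part company when multi-dose versus none is not significant and single dose versus none is. Nothing in the article says whether that result is a positive trial or an exploratory finding.

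The reverse direction matters too. The Discussion foresees spending on charcoal being diverted if it proves ineffective, so a false finding against a regimen would also have consequences.

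**Working it through.** **Inputs.** Deaths 10% versus 7%, alpha 5% (sidedness not given), power 80%, 1400 per arm (Sample size). Allocation: "to allocate patients in equal numbers to each treatment group i.e. ratio 1:1:1" (Randomisation). No inflation for attrition: "There should have been no loss to follow up for the primary outcome" (Sample size).

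**1. Reproduce the 1400.** With p̄ = 0.085,

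n = [z(1−α/2)·√(2p̄(1−p̄)) + z(power)·√(p1(1−p1) + p2(1−p2))]² / (p1−p2)²

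= [1.960 × 0.3944 + 0.8416 × 0.3938]² / 0.03² = 1.1045² / 0.0009, which rounds up to 1356.

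The continuity-corrected value is (n/4)·[1 + √(1 + 4/(0.03n))]² = 1422. The plan's 1400 lies between the two. Its power is Φ[(0.03·√1400 − 1.960 × 0.3944)/0.3938] = Φ(0.887) = 81.3%.

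Other alphas do not fit:

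| Alpha per comparison | n per arm (with continuity correction) | Power at 1400 |
|---|---|---|
| One-sided 5% | 1068 (1134) | not needed |
| Two-sided 5% | 1356 (1422) | 81.3% |
| Two-sided 2.5% (Bonferroni, two tests) | 1642 (1708) | 72.8% |
| Two-sided 1.67% (Bonferroni, three tests) | 1809 (1875) | 67.5% |

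So 1400 spends the whole two-sided 5% on one comparison.

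**2. What the 80% describes.** If both regimens truly give 7%, simulation with 1400 per arm puts the power at 81% for each comparison with no charcoal, 92% for at least one of them and 71% for both. The stated 80% is therefore the power of one comparison.

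**3. Error if every comparison is confirmatory at two-sided 5%.** This is an assumption. All three arms have the same 10% mortality. Two comparisons that share an arm have correlation 0.5, so both show a false benefit with probability 0.0046.

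- Any false difference, two charcoal-versus-none tests: 2 × 0.05 − 2 × 0.0046 = 0.0908, or 9.1%. Opposite-direction rejections are negligible.
- Any false difference, all three tests: 12.2% (studentized range for three groups; simulation agrees).
- False finding that at least one regimen reduces deaths compared with none: 2 × 0.025 − 0.0046 = 0.0454, about 4.5%.
- False single-dose benefit beside a non-significant multi-dose result: 0.025 − 0.0046 = 0.0204, about 2%.

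Treating the tests as independent would give 9.75% and 14.3%, which is too high because arms are shared.

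**4. Error if the order binds.** Test multi-dose versus none first, and go on only if it is significant.

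- If that null is true, any false claim must first reject it, which has probability of at most 5%.
- If it is false, single dose cannot equal both other arms, so at most one of the two remaining nulls is true, and it is tested at 5%.

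The overall error is therefore at most 5% in both cases, and the first test keeps its 81.3% power.

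**The case against.** The case on the other side has four parts, and much of it stands.

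- **Testing each comparison at 5% is not stated.** It is inferred from the sample size and the 95% intervals. A testing rule is commonly left to the analysis plan, which is not shown. This stands, so the absence of a multiplicity rule is not the point. The point is that the article itself gives two accounts of which claim carries the 5%.
- **A reader might infer that the trial has a 9–12% chance of falsely concluding that charcoal works.** The documents do not support that. Those figures count false harm, and the 12.2% also counts false differences between the two regimens. The false-benefit figure is about 4.5%. Nor is 9–12% the trial's actual error rate, because the unscheduled interim analyses in the IDMEC section are left out.
- **The article already has a hierarchy.** The main hypothesis and the Abstract's reason for the single-dose arm both put multi-dose versus none first. If only that comparison is confirmatory, the error is 5%. This also stands, but the hierarchy does not settle the matter while all three comparisons are called principal and two sections ask about either regimen.
- **Either regimen may mean each regimen separately, with 5% per comparison.** That is a legitimate reading, and whether distinct regimens sharing a control need joint error control is debated. The article should then say that the 5% is per comparison.

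**Conclusion.** The concern holds as an inconsistency about what the alpha and power refer to. It does not show that the sample size is wrong: 1400 per arm is adequate for one comparison at two-sided 5%.

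The 9.1% and 12.2% rest on three assumptions: no effect of either regimen, all comparisons treated as confirmatory at an unsplit two-sided 5%, and no interim looks. A misleading single-dose benefit beside a non-significant multi-dose result would arise by chance about 2% of the time, so the practical risk is modest. The change is still worth making, because the order already in the article can hold the overall error at 5% with no loss of power for the main hypothesis.

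**What to change.** 1. In Sample size, state that the 5% (two-sided) alpha and 80% power refer to multi-dose versus no charcoal.
2. Align the research question in Methods/design and the wording in Sample size with the main hypothesis.
3. Make the order binding. Test multi-dose versus none at two-sided 5%. Only if it is significant, test multi-dose versus single dose and single dose versus none, each at two-sided 5%. Otherwise report those two as estimates with 95% intervals.

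**Cost.** A few sentences and no extra patients. Splitting alpha instead would lower power at 1400 per arm to 73% or 67%, and recruitment has closed (more than 4500 patients), so the sample cannot be enlarged to make up for it. The real price is that single dose versus none, which is part of the stated research question, cannot be confirmatory if multi-dose versus none fails. That fits the authors' own expectation that a single dose would be less effective, but it should be said openly.

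**Timing.** The article reports that the final analysis is underway. The rule should be fixed and dated before arm-level results are seen, by people who have not seen the interim results.
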